## Abstract

**Background:**

The clinical diagnosis of atlantoaxial joint subluxation (AJS) in traditional Chinese medicine (TCM) is characterized by an unequal distance between the lateral mass of the atlas and the odontoid process on imaging, resulting in neck pain accompanied by symptoms such as dizziness, headache, and limited cervical mobility. In Shanghai, Shi cervical rotational manipulation (SCRM) is a commonly employed TCM manual therapy for treating this condition. Nevertheless, there is a lack of evidence-based medical information regarding the clinical efficacy and safety of this technique.

**Objective:**

The principal aim of this study is to evaluate the efficacy and safety of SCRM in patients diagnosed with AJS.

**Methods:**

This study is a prospective randomized controlled clinical trial that will be conducted at a single center and that has a follow-up period of 24 weeks. A total of 96 patients diagnosed with AJS will be recruited from outpatient and inpatient clinics at Shanghai Baoshan Hospital of Integrated Traditional Chinese and Western Medicine. These patients will be randomly assigned to either the experimental group (SCRM) or the comparison group (basic cervical manipulation [BCM]). Treatment sessions consisting of SCRM or BCM will be administered twice a week for a duration of 4 weeks. Clinical monitoring indicators include the presence or absence of clinical symptoms as recorded on a symptom recording form, cervical imaging examination findings using cervical computed tomography, degree of neck pain measured by a visual analog scale (VAS), cervical range of motion assessed through cervical mobility measurement, degree of vertigo evaluated using the Vertigo Symptoms Scale-Chinese Version (VSS-C), and adverse events that may occur during the follow-up period. The time points for data collection and follow-up are baseline and postintervention (weeks 4, 8, 12, 16, 20, and 24).

**Results:**

This paper presents an overview of the reasoning and structure of a prospective randomized controlled trial with the objective of investigating the clinical efficacy and safety of SCRM in patients with AJS by assessing improvements in clinical symptoms, neck pain severity, and vertigo severity and evaluating changes in cervical imaging findings. Recruitment was started in March 2023. By the end of May 2024, 76 patients were included in this project. The last follow-up data are predicted to be collected by the end of February 2025.

**Conclusions:**

This investigation will yield dependable evidence regarding the efficacy and safety of SCRM in patients with AJS.

**Trial Registration:**

Chinese Clinical Trial Registry ChiCTR2300068510; https://www.chictr.org.cn/showprojEN.html?proj=186883

**International Registered Report Identifier (IRRID):**

DERR1-10.2196/57865

## Introduction

Joint subluxation is a distinct medical diagnosis within the realm of traditional Chinese medicine (TCM) [1]. In November 2020, the National Health Commission of China and the China Administration of Traditional Chinese Medicine officially incorporated the term “joint subluxation” into the updated edition of the “International Classification of Diseases 11th Revision, ICD-11” instead of “Gu Cuo Feng,” which was previously widely used in TCM clinical diagnosis, thereby establishing its recognition as a universally accepted diagnostic term [2]. While joint subluxation can manifest in various articulations throughout the body, the spinal region, particularly the cervical spine, frequently serves as a prevalent site of occurrence [3]. Hence, in TCM diagnosis, the specific location of manifestation is referred to as joint subluxation of the site, with atlantoaxial joint subluxation (AJS) being a prevalent clinical condition. Meanwhile, AJS is also considered a type of cervical spondylosis. The primary visual indication of AJS is an asymmetrical gap observed between the lateral mass of the atlantoaxial joint and the odontoid process on cervical spine X-ray or computed tomography (CT) scans, along with misalignment of the axis of the spinous process relative to the midline of the spinous process [4].

The atlantoaxial joint, situated in the human cervical spine, functions as a relatively autonomous unit. Within this joint, the atlas assumes the role of the central axis for neck motion, contributing to over 40% of the rotational movement of the cervical spine. Conversely, the axis serves as the focal point for stress in the upper cervical spine and functions as a primary attachment site for the neck’s short muscles and ligaments [5]. In instances where the atlantoaxial joint experiences a pathological state known as “joint subluxation,” it can lead to the entrapment of the synovial membrane and joint capsule, resulting in localized swelling and pain in the cervical spine, impaired joint movement, and stimulation of the corresponding regions of the nerves, blood vessels, and receptors, which can cause symptoms such as vertigo and pain [6]. For a long time, AJS has been commonly referred to as atlantoaxial joint instability, atlantoaxial joint disorder, etc [7,8]. The clinical manifestations are mainly neck pain accompanied by dizziness, headache, and cervical limited mobility, and thus, clinicians previously used to diagnose patients as having cervical vertigo [9,10].

Cervical manipulation is a frequently employed approach in the management of cervical spondylosis, with cervical rotation manipulation or small joint mobilization being the most prominent technique [11,12]. This method involves the rotation of the subject’s head along the longitudinal axis of the cervical spine, resulting in an audible “clicking” sound from the cervical vertebra joint. The clinical use of this technique has garnered significant attention and has been supported by empirical evidence demonstrating its efficacy and safety through various studies. Studies have demonstrated that this technique has the potential to ameliorate the pathological condition of joint subluxation, restore bones and joints to their typical physiological and anatomical alignments, and re-establish dynamic and static mechanical equilibrium in the cervical vertebra joint, thereby accomplishing therapeutic objectives [13-15]. Nevertheless, variations in clinical effectiveness arise due to divergent approaches to manipulation and the focus of the manipulation on the atlantoaxial joint, a crucial anatomical region within the cervical spine, and the safety of manual therapy has always been a concern of clinicians [16,17].

Shi cervical rotational manipulation (SCRM) is a technique for treating AJS created by Shi’s Traumatology TCM Academic School, which is the largest traumatology school of TCM in Shanghai. The technical attributes of SCRM encompass the swift application of stress, which belongs to the high velocity and low amplitude (HVLA) technique. In our prior investigation, we formulated a standard operating procedure (SOP) for SCRM, which will be explained subsequently [18]. Our research team quantified objective metrics and kinematic and kinetic parameters pertaining to the technique, considering the viewpoints of both recipients and practitioners [19]. Furthermore, we assessed the safety of the technique through finite element analysis and provided preliminary insights into its biomechanical mechanism of action [20]. Regarding the clinical assessment of the immediate efficacy of SCRM, a 50% reduction in visual analog scale (VAS) scores was observed immediately following the procedure. Additionally, approximately 70% to 80% of participants reported subjective improvements such as a sensation of a lighter head, a relaxed neck, and brighter eyes [18]. These findings suggest the significant immediate efficacy of the SCRM technique. In our subsequent short-term and medium-term clinical follow-up study in which we applied SCRM to treat patients with cervical spondylotic radiculopathy, the intervention had an efficacy rate of 94.74%. Furthermore, the overall efficacy rate at 3 months was 89.47%, with no notable discomfort or adverse events reported [18]. Nonetheless, there is still a lack of standard randomized controlled studies on SCRM, and there is limited evidence-based medical information on the efficacy and safety of SCRM. Consequently, the aim of this randomized controlled trial is to assess the efficacy and safety of SCRM in patients with AJS.

## Methods

### Study Design

This study will be a single-center, prospective, randomized controlled clinical trial to evaluate the effectiveness and safety of SCRM in patients with AJS. We have used the SPIRIT (Standard Protocol Items: Recommendations for Interventional Trials) reporting guidelines to introduce this protocol [21]. A total of 93 participants with AJS from outpatient and inpatient clinics will be recruited and randomly allocated to either the SCRM group or the basic cervical manipulation (BCM) group. Screening (visit 0) will be performed within 3 days prior to enrollment to assess eligibility and collect baseline data and imaging data. Those participants who meet the inclusion criteria will be randomly assigned to the SCRM group or BCM group and receive the corresponding treatment of each group twice a week for 4 weeks. After the end of treatment (visit 1), all patients will undergo evaluations, including assessment of symptoms and signs, cervical mobility examination and measurement, assessment of VAS scores and Vertigo Symptoms Scale-Chinese Version (VSS-C) scores, imaging, efficacy evaluation, and assessment of adverse events. Then, all patients will be followed up every 4 weeks until the end of the study at 24 weeks. Additionally, imaging and efficacy evaluations will be conducted at week 4 (visit 1) and week 24 (visit 6), and assessment of the VSS-C score will be conducted at week 4 (visit 1), week 16 (visit 4), and week 24 (visit 6). The flowchart schedule is shown in Table 1, and the flow diagram of participants is shown in Figure 1.

**Table 1 table1:** Flowchart schedule.

Assessment	Time window						
	Visit 0 (screening stage; –3 to 0 days)	Visit 1 (week 4)	Visit 2 (week 8)	Visit 3 (week 12)	Visit 4 (week 16)	Visit 5 (week 20)	Visit 6 (week 24)
Baseline information	Yes	No	No	No	No	No	No
Basic medical history and drug combination	Yes	No	No	No	No	No	No
Inclusion and exclusion criteria	Yes	No	No	No	No	No	No
Informed consent	Yes	No	No	No	No	No	No
Randomization allocation	Yes	No	No	No	No	No	No
Symptoms and signs	Yes	Yes	Yes	Yes	Yes	Yes	Yes
Cervical mobility examination and measurement	Yes	Yes	Yes	Yes	Yes	Yes	Yes
VAS^a^ score	Yes	Yes	Yes	Yes	Yes	Yes	Yes
VSS-C^b^ score	Yes	Yes	No	No	Yes	No	Yes
Imaging (CT^c^ or X-ray)	Yes	Yes	No	No	No	No	Yes
Efficacy evaluation	No	Yes	No	No	No	No	Yes
Adverse events	No	Yes	Yes	Yes	Yes	Yes	Yes

^a^VAS: visual analog scale.

^b^VSS-C: Vertigo Symptoms Scale-Chinese Version.

^c^CT: computed tomography.

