### Exclusion Criteria

The exclusion criteria are as follows: (1) cervical spondylosis of the nerve root type or spinal cord type and severe spinal stenosis; (2) a history of spinal surgery or severe spinal trauma; (3) a history of congenital variation or malformation of an unstable cervical vertebral structure; (4) dizziness or vertigo caused by other diseases diagnosed by specialized examinations such as those performed by cardiovascular, otolaryngology, and neurology departments; (5) imaging findings, including spinal infection, fracture, tumor, tuberculosis, severe spinal deformity, severe osteoporosis, ankylosing spondylitis, and osteitis deformans; (6) severe primary diseases of the endocrine system, cardiovascular system, and autoimmune system, and tumor or mental illness; (7) pregnancy and breastfeeding; and (8) no acceptance of cervical manipulation therapy.

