### Sample Size

The sample size calculation is based on our previous clinical research in patients with cervical spondylosis of the nerve root type, using the same primary outcome instrument. The efficiency of SCRM is 89.5%, while that of BCM is 54.6%. The sample size calculation formula is as follows:

The α is .05 and 1–β is .90. According to estimations, 48 participants per group are needed considering that this is a long-term follow-up that is expected to have a dropout rate of no greater than 20%.

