## Results

This paper presents an overview of the reasoning and structure of a prospective randomized controlled trial with the objective of investigating the clinical efficacy and safety of SCRM in patients with AJS by assessing improvements in clinical symptoms, neck pain severity, and vertigo severity and evaluating changes in cervical imaging findings. Recruitment was started in March 2023. By the end of May 2024, 76 patients were included in this project. The last follow-up data are predicted to be collected by the end of February 2025. The findings of this study are expected to be submitted for publication in late 2025.

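### Study Design recruits 93 patients, but the Abstract says 96 and the Sample Size section needs 48 per group; the calculation supports 96, and its 90% power depends on rates carried over from an excluded population

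*Protocol article*

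**What the plan says.** The recruitment total appears in three places in the protocol article.

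- Abstract, Methods: "A total of 96 patients diagnosed with AJS will be recruited".
- Methods, Study Design: "A total of 93 participants with AJS from outpatient and inpatient clinics will be recruited".
- Methods, Sample Size: "48 participants per group are needed", after allowing for dropout of up to 20%.

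The Sample Size section assumes efficacy of 89.5% with SCRM and 54.6% with BCM, α of .05 and power of .90. It says the calculation is "based on our previous clinical research in patients with cervical spondylosis of the nerve root type" and gives as its reason that the primary outcome instrument was the same. Exclusion criterion 1 rules out "cervical spondylosis of the nerve root type or spinal cord type and severe spinal stenosis".

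For the earlier radiculopathy study, the Introduction reports one efficacy rate of 94.74% with no time point, and then "the overall efficacy rate at 3 months was 89.47" (per cent). In this trial, Study Design, Table 1 and the Primary Outcome section place the efficacy evaluation at week 4 and week 24 only. The Statistical Analysis section fixes a one-sided superiority test at α = .05. The Discussion (Findings and Strengths) describes the sample size as accurately determined from the prior research.

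**The concern.** A target enrolment should have one value. The count given in Results, 76 patients by the end of May 2024, is below both totals. On the text as it stands, closing recruitment at 93 and closing it at 96 would each comply with one section and depart from another. The final report could then not show plainly that the planned size was reached.

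The secondary matter is what the stated power rests on. Both planning rates come from patients who cannot enter this trial, and at least one of them seems to belong to a time point at which this trial does not evaluate efficacy. The Discussion's claim of accuracy is stronger than that basis allows.

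**Working it through.** **1. Which total does the calculation support?** Inputs from Sample Size: p1 = 0.895, p2 = 0.546, difference d = 0.349, mean p̄ = 0.7205, α = .05, power .90, dropout 20%. The formula is not visible in the text at hand, so I tried the usual variants.

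Pooled-variance formula: n = [z_α √(2p̄(1−p̄)) + z_β √(p1(1−p1) + p2(1−p2))]² / d²

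Continuity correction: n_c = (n/4) × [1 + √(1 + 4/(n d))]²

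Here √(2p̄(1−p̄)) = 0.6346, √(p1(1−p1) + p2(1−p2)) = 0.5847 and d² = 0.1218.

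- Two-sided: n = (1.960 × 0.6346 + 1.2816 × 0.5847)² / 0.1218 = 32.62, and n_c = 38.13. Dividing by 0.8 gives 47.66, so **48 per group, 96 in total**. Rounding 38.13 up to 39 first would give 49.
- One-sided: n = 26.40, rounded to 27, then 27/0.8 gives 34 per group (68 in total). With continuity correction n_c = 31.87, rounded to 32, then 32/0.8 = 40 per group (80 in total).

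The stated 48 is therefore reproduced by the two-sided, continuity-corrected version, and 2 × 48 = 96. No variant leads to 93. Multiplying by 1.2 instead of dividing by 0.8 takes 2 × 39 to 93.6, which is close, but that would round up to 94 and would contradict the 48 per group printed in the same section.

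**2. What does the choice between 93 and 96 cost?** Normal-approximation power at the planned rates, one-sided .05: Φ{[d√n − z_α × 0.6346] / 0.5847}.

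| Total | Per group, no loss | Power | Per group after 20% loss | Power |
|---|---|---|---|---|
| 96 | 48 | 99.1% | 38.4 | 97.2% |
| 93 | 46.5 | 98.9% | 37.2 | 96.8% |

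With a two-sided .05 test the figures after loss are 94.2% and 93.5%. The difference is below 1 point in every case.

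**3. The planning rates.** The population in Sample Size (nerve root type) is the one named in exclusion criterion 1. The 89.5% equals the Introduction's 89.47% after rounding, and no other SCRM efficacy rate in the article matches it, so 3 months is the likely time point. Whether counted from the start or the end of treatment, 3 months falls near week 12 or week 16, and Table 1 has no efficacy evaluation at either. No time point is given anywhere for the BCM rate of 54.6%.

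**4. How sensitive is the power?** Exact power of the chi-square test, obtained by summing binomial probabilities over all outcomes with z ≥ 1.645, with 38 evaluable per group (48 × 0.8 = 38.4) and the one-sided .05 test of the Statistical Analysis section. The article gives no rates for AJS, so every row after the first is an assumption.

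| SCRM vs BCM | Power |
|---|---|
| 89.5% vs 54.6% (plan) | 97.4% |
| 89.5% vs 60% | 92.7% |
| 85% vs 54.6% | 91.3% |
| 89.5% vs 65% | 83.9% |
| 80% vs 55% | 77.5% |
| 85% vs 65% | 65.5% |

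**The case against.** Three patients in 96 is 3%, and step 2 shows that the statistical effect is negligible, so this can fairly be called a slip in one number. That stands as to size. It does not remove the contradiction, because the 93 is in the main Methods text and is given as the number recruited and randomised, not as an evaluable number after dropout.

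The borrowed population is disclosed in the Sample Size section with a reason, and planning from the nearest available data is normal practice. That also stands: it calls for a caveat and is not an arithmetic error. The 3-month link is an inference from matching figures and covers only the SCRM rate.

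Four stronger readings are tempting, and the document does not support them.

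- A reader might infer that 90% power is lost unless AJS patients respond exactly like the excluded group. The table in step 4 shows otherwise: power stays above 90% at 85% vs 54.6% and at 89.5% vs 60%.
- A reader might test sensitivity two-sided, which gives about 75%, 66% and 53% for the last three rows. The planned test is one-sided, so those figures understate its power by 9 to 12 points.
- A reader might infer from the recruitment pace that 93 is the true target, since Results says "The last follow-up data are predicted to be collected by the end of February 2025". To complete 24 weeks by 28 February 2025 the last patient must enter by 13 September 2024, 105 days after 31 May. At the average pace so far, 17.5 to 18.7 patients are expected in that window (for a start between 1 and 31 March 2023). The 93 target needs 17 more and the 96 target needs 20. Under a Poisson count the chance of 20 or more is 30% to 41%, so a predicted date cannot separate the two totals.
- A reader might see two stopping points or an interim decision. The article describes no interim look or stopping rule; there are simply two recruitment totals.

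**Conclusion.** The contradiction is certain: 93 in Study Design against 96 in the Abstract and 48 per group in Sample Size. The figure to correct is 93, because 48 per group follows from the stated inputs. That rests on the two-sided, continuity-corrected variant having been used, which the visible text cannot confirm; but the 48 per group is printed and does not depend on it. The effect on power is under 1 point. The correction is needed so that the protocol carries a single recruitment commitment, not because the trial would be underpowered at 93.

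The secondary point holds as a caveat. The stated 90% power is conditional on rates from a population that this trial excludes, with the SCRM rate probably measured at 3 months. Under the planned one-sided test there is a margin at those rates (97.4% with 38 evaluable per group), and 90% survives moderate departures from them. It does not survive larger ones: power falls to between 65.5% and 83.9% for the last three assumed pairs. Nothing in the article shows which pair is closest to the truth for AJS.

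**What to change.** 1. In Study Design, change 93 to 96 and add that this is 48 per group, in line with the Abstract and Sample Size.
2. In Sample Size, state that the 90% power is conditional on 89.5% vs 54.6% carried over from nerve-root-type patients, who are not eligible here. Give the time point of each rate, and say why they are taken to apply at week 4 or week 24.
3. If a sensitivity range is added, compute it for the one-sided .05 test and label the alternative rates as assumptions; the table above can serve.
4. In the Discussion, replace the claim that the size was accurately determined with the same conditional statement.

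The predicted date of last follow-up need not change on this account. The cost is four text edits and a more guarded power statement, with no patients beyond the 96 already planned.

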**Figure 1 figure1:**
[figure not shown]
Flow diagram of participants. AJS: atlantoaxial joint subluxation; BCM: basic cervical manipulation; CT: computed tomography; SCRM: Shi cervical rotational manipulation; VAS: visual analog scale; VSS-C: Vertigo Symptoms Scale-Chinese version.

The Shanghai Baoshan Hospital of Integrated Traditional Chinese and Western Medicine will be responsible for the recruitment, screening, and intervention of all participants and the assessment of all outcomes. Management of the randomization sequence and data analyses will be carried out by the Institute of Traumatology, Shi’s Center of Orthopedics and Traumatology, Shuguang Hospital Affiliated to Shanghai University of Traditional Chinese Medicine.

### Participants

Patients who are aged between 18 and 70 years with AJS will be included in the study. The screening, inclusion, and exclusion procedures for all patients; the notification and signing of informed consent; and the documentation of each follow-up visit will be meticulously recorded on an individual basis.

### Diagnostic Criteria

The diagnosis of AJS is based on the Diagnostic Criteria for Traditional Chinese Medicine and the International Classification of Diseases 11th Revision (ICD-11), and several aspects are considered. First, the patient has a history of neck strain or injury and has a long-term habit of working or living with a low head. Second, the clinical manifestations are mainly vertigo, dizziness, headache, and soreness in the neck. Third, the cervical movement is mainly limited to the left-right rotation of the atlantoaxial joint. When performing palpation, the muscle tension around the atlantoaxial joint increases or small blocky or strip-shaped muscle nodules are felt, which may induce or exacerbate dizziness or vertigo. Fourth, cervical X-ray or CT shows an asymmetrical gap between the lateral mass of the atlantoaxial joint and the odontoid process, with a difference of more than 2 mm, along with the misalignment of the axis of the spinous process relative to the midline of the spinous process.

### Inclusion Criteria

The inclusion criteria are as follows: (1) meeting the diagnostic criteria of AJS; (2) male or female sex and age of 18 to 70 years; (3) recurrent clinical symptoms, such as neck pain, vertigo, dizziness, and headache, for less than 4 weeks, which cannot be relieved; and (4) voluntary participation in this trial and signing of the informed consent document.

